# Structural and functional brain biomarkers of clinical response to rTMS of medication-resistant auditory hallucinations in schizophrenia patients: study protocol for a randomized sham-controlled double-blind clinical trial

**DOI:** 10.1186/s13063-019-3311-x

**Published:** 2019-04-23

**Keywords:** Schizophrenia, auditory verbal hallucinations, non-invasive brain stimulation, repetitive transcranial magnetic stimulation, clinical response, predictive biomarkers, structural connectivity, functional connectivity, clinical trial

## Abstract

**Background:**

The potential of non-invasive repetitive transcranial magnetic stimulation (rTMS) to improve auditory verbal hallucinations (AVH) in schizophrenia patients has been increasingly explored over the past decade. Despite highly promising results, high inter-individual variability of clinical response and ineffective outcomes in a significant number of patients underscored the need to identify factors associated with the clinical response to rTMS. It should help improve the efficacy of rTMS in patients with medication-resistant AVH, and allow a better understanding of its neural impact. Here, we describe an exploratory study protocol which aims to identify structural and functional brain biomarkers associated with clinical response after an rTMS treatment for medication-resistant AVH in schizophrenia.

**Methods:**

Forty-five schizophrenia patients with medication-resistant AVH will be enrolled in a double-blind randomized sham-controlled monocentric clinical trial. Patients will be assigned to a regime of 20 sessions of active or sham 1 Hz rTMS delivered twice a day, 5 days a week for 2 weeks over the left temporo-parietal junction. Response will be assessed after rTMS and patients will be classified in responders or non-responders to treatment. Magnetic resonance imaging (MRI) sessions including diffusion weighted imaging and resting-state functional MRI sequences will be recorded before the onset of the rTMS treatment and 3 days following its discontinuation. The primary outcome measure is difference in fractional anisotropy between responder and non-responder patients at baseline. Differences in resting-state functional MRI data at baseline will be also investigated between responder and non-responder groups. Clinical, neuropsychological, neurophysiological, and blood serum BDNF assessments will be performed at baseline, 3 days, 1 month, and 3 months following rTMS.

**Discussion:**

The aim of this research project is to identify and assess the biomarker value of MRI-based structural and functional biomarkers predicting clinical response to rTMS for AVH in schizophrenia patients. The outcome of the trial should improve patient care by offering them a novel suitable therapy and deepen our understanding on how rTMS may impact AVH and develop more effective therapies adapted to individual patient needs.

**Trial registration:**

ClinicalTrials.gov, NCT02755623. Registered on 22 April 2016.

**Electronic supplementary material:**

The online version of this article (10.1186/s13063-019-3311-x) contains supplementary material, which is available to authorized users.

## Background

Schizophrenia has been conceptualized as a brain connectivity disorder, which would be the cause of the main symptoms of the pathology [1, 2]. Auditory verbal hallucinations (AVH) are the hallmark symptom of schizophrenia, present in 70–80% of patients [3, 4] and have been linked to alterations in structural and/or functional interactions. In the structural domain, alterations of white matter integrity in the left arcuate fasciculus and interhemispheric projections via the corpus callosum have been associated with AVH in schizophrenia patients [5, 6]. Additionally, in the functional domain, deficits of resting-state functional connectivity have been reported for left fronto-temporal interactions, across nodes of the Default Mode Network (DMN) and also between DMN and Salience Network regions, and have been associated with AVH severity [6–10]. In line with the concept of altered connectivity, treatments with the ability to modulate local brain activity and network functional connectivity could serve to normalize dysfunction in perturbed networks, improving AVH severity.

Repetitive transcranial magnetic stimulation (rTMS) is a non-invasive brain stimulation technology with the ability to modulate the activity of directly targeted cortical areas and their associated networks [11]. Widely used over the last two decades in exploratory, diagnostic, and therapeutic applications, rTMS has shown a promising potential for restoring abnormal functional connectivity patterns underlying pathology. Several meta-analyses have demonstrated that low-frequency rTMS patterns delivered to the left temporoparietal junction (TPJ) significantly reduced AVH in schizophrenia [12–19]. However, the clinical benefit of this therapy remains moderate and is characterized by a high degree of interindividual variability. Indeed, a large number of patients appear to respond poorly, exhibiting no significant improvement in AVH rates [16].

Variability of clinical response to rTMS has been explained by brain connectivity differences subtending functional [20] and/or structural [21–23] interactions. Nonetheless, to date, very few studies have aimed to further characterize the detailed determinants of this variability. A better understanding of this phenomena bears the potential to increase the effectiveness of rTMS-based treatments and promote the development of individualized therapeutic approaches tailored to the specificities of each patient. The identification of predictive and explanatory biomarkers of clinical response to rTMS is an expanding domain with the potential to improve therapeutic plans offered to patients, while improving our understanding of underlying rTMS mechanisms on pathological symptoms such as AVH. Herein, we will test the impact of active rTMS 1 Hz stimulation delivered to the left TPJ on AVH severity scores and use such outcomes to quantify interindividual clinical response variability and test the predictive and explanatory value of a series of magnetic resonance imaging (MRI)-based functional and structural biomarkers assessing interregional interactions. A large battery of clinical, neuropsychological, and motor excitability neurophysiological assessments as well as molecular biology serum assays will be performed in parallel to better understand the determinants of AVH in schizophrenia and pinpoint rTMS therapeutic mechanisms. We hypothesize that rTMS treatment for AVH will show large interindividual response variability, providing a unique opportunity to identify MRI-based structural and functional connectivity biomarkers of positive clinical response to focal neurostimulation.

## Aims and hypotheses

The main objective of this trial is to identify whether the clinical response to rTMS for AVH in schizophrenia patients could be driven by distinct brain connectivity patterns. The clinical response to rTMS is defined as a decrease of 50% or more in the Hallucinations Change Score (HCS) at the end of the active rTMS stimulation (week 3 (W3)) from the baseline (W0) value. We sought to determine whether structural (arcuate fasciculus and corpus callosum) and functional (frontal-temporo-parietal network and the DMN) connectivity differences in AVH-related networks may influence the therapeutic effect of rTMS. These differences may explain why some patients do not respond to active rTMS treatment while others do. We hypothesize that structural and functional connectivity in AVH-related networks would be distinct between schizophrenia patients who respond to rTMS and those who do not.

In a second aim, given rTMS can modulate the resting-state functional connectivity between frontal and temporo-parietal cortices in schizophrenia related to improvements in AVH [9, 24], we sought to evaluate whether there are functional connectivity changes in schizophrenia patients associated with clinical improvement following the rTMS treatment. We hypothesized that functional connectivity changes after rTMS treatment will be only observed in schizophrenia patients who respond clinically to active rTMS (with a reduction of AVH), but not in those who do not.

## Methods/design

### Study design

This is a randomized, sham-controlled double-blind, monocentric study. Patients will be randomly assigned to one of two arms, either active rTMS or sham rTMS applied to the left TPJ of each patient. Twenty sessions of rTMS treatment will be administered daily (from Monday to Friday, weekends off) at a frequency of 1 Hz for a period of 2 weeks. Clinical, neuropsychological, neurophysiological, and biological evaluations will be carried out before regime onset (W0), on the week following the end of rTMS treatment (W3), and at 1 (W7) and 3 months (W15) after the termination of rTMS treatment. MRI sequences will be recorded at W0 and W3. The first MRI acquisition will be recorded on the Friday of W0 (3 days before rTMS treatment) and the second on the Monday of W3 (3 days after rTMS treatment). Figures 1 and 2 show the experimental design. The protocol study follows the SPIRIT recommendations. For the SPIRIT checklist see Additional file 1.

**Fig. 1 Fig1:**
[figure not shown]
Flow chart of the study design

**Fig. 2 Fig2:**
[figure not shown]
Description of the enrolment, treatment, and assessments during the study protocol *AHRS* Auditory Hallucinations Rating Scale, *BDI* Beck Depression Inventory, *BDNF* brain-derived neurotrophic factor, *HCS* Hallucination Change Score, *MRI* magnetic resonance imaging, *PANSS* Positive And Negative Syndrome Scale, *MEP* motor-evoked potentials, *PSYRATS* Psychotic Symptom Rating Scale, *rTMS* repetitive transcranial magnetic stimulation, *t* time point, *W* week.

### Study setting

This trial will be conducted by the Unité de Recherche Clinique of the Etablissement Public de Santé Ville-Evrard (Neuilly-sur-Marne, France). All assessments and rTMS interventions will be performed at the Unité de Recherche Clinique of the Établissement Public de Santé Ville-Evrard. The MRI acquisitions will be performed at the Center for Neuroimaging Research at the Institut du Cerveau et de la Moelle Epinière (Paris, France).

### Participants

#### Recruitment

Participants will be enrolled through psychiatric services of the Établissement Public de Santé Ville-Evrard, hospitals of the region Ile-de-France (within and around Paris, France) and referral by medical practitioners or therapists. The choice of rTMS treatment for schizophrenia patients will be decided by their clinician consultant. Following verification of the eligibility criteria by researchers, patients wishing to participate in the protocol will be included in the study.

#### Inclusion criteria

Patients will have to be diagnosed with schizophrenia according to DSM-5 (Diagnostic and Statistical Manual of Mental Disorders, 5th edition) criteria, suffer from medication-resistant AVH, demonstrate clinical stability for at least 3 months, be aged between 18 and 65 years old, and be right-handed. Medication refractoriness is defined as a failure of treatment with two different antipsychotic drugs, of which at least one is considered atypical. Patients and their physicians will be strongly instructed not to modify the pharmacological treatment right before or throughout participation in the study. Additionally, patients will have to have sufficient knowledge of the French language. All participants of the study will be asked to sign an informed consent form.

#### Non-inclusion criteria

Patients presenting with at least one of the following criteria are not to be enrolled in the study: (1) major psychiatric disorders other than schizophrenia according to DSM-5 criteria; (2) indulging in an addiction (alcohol, psychoactive substances) over the last 12 months; (3) having received rTMS treatment in the last 12 months; (4) participating in a concurrent research protocol; (5) a history of seizures; (6) having any contraindication for rTMS (patient with epilepsy, brain surgery and/or head trauma in the past, use of cardiac pacemaker, or surgical staples on the scalp); (7) having potential contraindications to MRI, e.g. pregnancy or lactating (a negative pregnancy test will be required if the patient is a female in reproductive years who does not use contraception), use of a cardiac pacemaker or surgical staples, patients suffering a neurological disorder, head trauma or claustrophobia; (8) patients with severe cardiovascular disease; (9) patients with medication which could decrease the epileptic threshold (bupropion, methadone, and theophylline); and (10) patients placed in psychiatric care either by the state or a third party.

#### Exit criteria

Patients will be withdrawn from the trial if (1) they simply wish to stop participation; (2) they could not undergo the first MRI session; (3) they did not complete the rTMS sessions; and (4) if they suffered from worsening symptoms.

### Interventions

#### Active rTMS protocol

Sessions of rTMS treatment will be carried out with a standard 70 mm figure-of-eight coil (Active Air Film coil, Magstim, Wales, UK), attached to a Magstim Rapid^2^ Stimulator (Magstim, Wales, UK). Participants will be randomly allocated to either the active rTMS (*n* = 35 patients) or to the sham rTMS (*n* = 10) groups. For both groups, the treatment will be administered in two consecutive sessions of rTMS, each delivered for 20 min and interleaved by a stimulation-free 1 h interval. All patients will receive twice-daily rTMS sessions over a period of 2 weeks (from Monday to Friday, weekends off), and therefore accrue a total of 20 rTMS stimulation sessions. The rTMS parameters that will be used are a frequency of 1 Hz (1 pulse per second), an intensity of 100% of the motor threshold (MT), and 1200 continuous pulses per session (thus 2400 pulses per day and 24,000 pulses in total for the whole treatment). The MT is defined as the minimal TMS intensity required to elicit motor evoked potentials (MEPs) measured with electromyographic (EMG) surface electrodes placed on the first dorsal interosseous hand muscle, of at least 50 μV peak-to-peak amplitude, at rest, in 5 out of 10 consecutive trials. The rTMS coil will be applied over the left TPJ, which will be targeted using established spatial coordinates for the Wernicke’s area in the left TPJ (Montreal Neurological Institute (MNI) coordinates: x = − 69, y = − 41, z = 11) [25]. This brain area will be labeled on a 3D rendering of the patient’s individual T1 MRI sequence on each patient. The TMS coil will be positioned tangential to the scalp location overlying the left TPJ using an MRI-based frameless stereotactic neuronavigation system (Brainsight, Rogue Research Inc., Montreal, Canada) (Fig. 3).

**Fig. 3 Fig3:**
[figure not shown]
TMS-targeted region and coil placement. The left TPJ will be targeted using established spatial coordinates for the Wernicke’s area in the left TPJ (Montreal Neurological Institute (MNI) coordinates: x = − 69, y = − 41, z = 11; Hoffman et al. [25]). Axial (a), coronal (b), and sagittal (c) MRI views of the location for the TMS targeted left TPJ are shown in this figure. This brain area will be labeled on a 3D rendering of the patient’s individual T1 MRI sequence on each patient. The TMS coil will be positioned tangential to the scalp location overlying the left TPJ using an MRI-based frameless stereotactic neuronavigation system (d and e)

#### Sham rTMS protocol

The sham TMS treatment condition will be strictly identical to the active treatment condition thanks to the use of a sham TMS coil (Sham Air Film coil, Magstim, Wales, UK). The sham rTMS coil is indistinguishable in terms of general appearance and shape from an active coil, and able to emulate periodic noise and scalp tactile sensations similar to those produced during the active TMS session for rTMS naïve patients or even experienced healthy subjects [26]. Moreover, this coil has a magnetic shield that reduces the diffusion of the magnetic field under its surface, stimulating only scalp skin receptors or superficial muscles, without inducing any significant physiological transcranial effect on the brain. The two rTMS conditions will be performed in parallel in separate subsets of patients; therefore, patients and evaluators will not be able to differentiate between active and sham stimulation.

### Imaging acquisition

Before and after the TMS therapy, MRI scans will be obtained in all participants on a 3 Tesla scanner (Siemens Healthcare, Erlangen, Germany). To characterize brain structure and navigate the rTMS coil location, we will record three-dimensional, high-resolution, isovoxel, T1-weighted brain volumes acquired with the following parameters: 256 × 240 × 176 matrix size with 176 contiguous slices, field of view (FOV) = 256 mm, 1 mm isotropic resolution, sagittal slice orientation, repetition time (TR) = 2300 ms, and echo time (TE) = 2.98 ms.

To characterize the structural connectivity, diffusion-weighted images (DWIs) will be obtained using a DWI sequence (104 × 104 × 84 matrix size with 60 contiguous slices, FOV = 208 mm, 2 mm isotropic resolution, transversal slice orientation, flip angle = 90°, TR = 3800 ms, TE = 86 ms). The encoding protocol will include 64 different non-collinear directions (gradient factor b = 1500 s/mm^2^) and one image without diffusion weighting used as the reference volume (b = 0 s/mm^2^, b0 image).

To characterize functional connectivity (resting-state functional MRI or rs-fMRI), we will record T2*-weighted MRI sequence applied with an echo-planar gradient (192 × 192 × 162 matrix size with 45 contiguous slices, FOV = 192 mm, 3 mm isotropic resolution, 20*%* interslice gap, transversal and coronal slice orientation, flip angle = 80°, TR = 2500 ms, TE = 30 ms) when subjects are resting while keeping their eyes closed. Patients are instructed to relax, remain still, and not to fall asleep.

After each MRI scan, we will also debrief with patients to investigate and document whether patients experienced hallucinations during the MRI sessions, and if so, in which sensory modalities and during which MRI sequences those might have occurred.

### Outcome measures

#### Primary outcome measures

Our primary aim is to identify brain connectivity differences between patients ‘responders’ and ‘non-responders’ to rTMS treatment. To cluster patients as ‘responders’ or ‘non-responders’, the clinical response to rTMS will be defined as a decrease of 50% or more in the HCS from baseline (W0) at the end of the active rTMS stimulation (W3). This definition is similar to that employed in previous studies [27, 28]. The HCS is described in the Clinical assessments section in the Secondary outcome measures paragraph and will allow analysis of the dataset in search of biomarkers associated with rTMS response, in particular structural and functional connectivity biomarkers.

To identify structural connectivity biomarkers to rTMS therapeutic response, we will compare DWI datasets, acquired at baseline, between ‘responder’ and ‘non-responder’ patients to rTMS. More precisely, we will consider fractional anisotropy (FA) levels along tracts of interest that will be reconstructed from probabilistic tractography algorithms. FA levels will be obtained at several equidistant points along the tract of interest [29]. This procedure will allow evaluation of the existence of global or focal (close to the stimulation site) white matter integrity alterations between ‘responders’ and ‘non-responders’. Tracts of interest will include the fasciculi that are involved in the language network (connections between TPJ and Broca areas, so called the arcuate fasciculi on each hemisphere, and transcallosal connections between the TPJ or Broca areas), and those that are part of the DMN (connections between the superior parietal cortex and prefrontal areas within each hemisphere; transcallosal connections between superior parietal cortex or prefrontal areas). FA values along each tract will be obtained at baseline (W0) and after rTMS treatment (W3) for ‘responders’ and ‘non-responders’.

To identify functional connectivity biomarkers to rTMS response, we will compare functional volumes, obtained at baseline and at rest, between ‘responders’ and ‘non-responders’. We will consider the connectivity strength between areas of networks of interest. Connectivity strength is the degree of dependence between the time courses of two areas (measured with a Pearson coefficient [30] or using dynamic causal modeling (DCM) [31]). The networks of interest will include the DMN (bilateral anterior cingulate cortex, bilateral prefrontal areas, bilateral superior parietal areas, bilateral precuneus) and the language network (bilateral TPJ, Broca areas). Connectivity strength between areas of these two networks will be obtained at baseline (W0) and after rTMS treatment (W3) in ‘responders’ and ‘non-responders’.

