### Statistical analysis

#### Sample size

The aim of this trial is to investigate the difference in brain functional and structural connectivity in schizophrenia patients receiving an active rTMS treatment and clinically responding to it or not as assessed by an amelioration of their AVH symptoms. Therefore, the sample size was calculated to determine the number of patients to be included in the active rTMS group on the basis of the primary outcome, namely the difference in FA values at baseline between ‘responders’ and ‘non-responders’. Unfortunately, no study provides a significant difference of rs-fMRI measures or FA values for a given tract (such as the left arcuate fasciculus) before and following a clinically effective versus a non-clinically effective rTMS treatment in schizophrenia patients, which would allow us to accurately estimate the adequate sample size for our trial. Nonetheless, FA values are highly reproducible and have a reliable estimation of variance. Therefore, we focused on FA values to determine sample size. Therefore, on the basis of a significant difference in the FA values between schizophrenia patients and healthy subjects for the left arcuate fasciculus [51] and assuming an α risk of 0.05 and a 1-β power of 0.80, we estimated the need to include 32 patients for the active rTMS group. To overcome an estimated 10% drop-out, we increased our recruitment needs for active rTMS group to 35 patients. Given a proportion of ‘responders’ and ‘non-responders’ to rTMS treatment as the one we propose for AVH in schizophrenia estimated at 40% and 60%, respectively [52], we will divide our cohort into 14 ‘responders’ and 21 ‘non-responder’ patients. According to a prior study [22], a minimum of 14 participants per group (‘responders’ or ‘non-responders’) has been deemed sufficient to conduct statistical analysis in neuroimaging and detect a significant effect of rTMS on brain structural connectivity. Moreover, a sham rTMS group of 10 patients will be followed in parallel to control for the placebo rTMS effect on AVH. As a result, the total number of participants required for the study is of 45 patients.

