Once tracts are reconstructed, one complementary measure will be considered. FA values will be measured along the tracts of interest. Along-tract measures of FA will be obtained on the basis of B-spline resampling of the fibers and averaging the FA values for each individual fiber on a given location (elastic model with 30 points in space at analogous anatomical locations in each individual) [29]. For instance, for the language network, the posterior location will be defined on the ROI of the TPJ, whereas the anterior location will be defined as the level of the ROI of the Broca areas. Mean FA values will be calculated at each point of the mean fiber along the *y* axis to check for local differences at specific points of the tract. A linear mixed-effects model will be applied serially for each tract and permutation methods will be performed to adjust the *p* values and control the Type 1 error.

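### The along-tract FA analysis is said to separate global from focal differences, but the only localisation step described is a check at each of 30 points, which cannot show that a difference varies along the tract

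*Protocol article*

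**What the plan says.** The abstract names the primary outcome: "The primary outcome measure is difference in fractional anisotropy between responder and non-responder patients at baseline". Under Primary outcome measures, FA is to be sampled at equally spaced positions along each tract, and a purpose is attached: "This procedure will allow evaluation of the existence of global or focal (close to the stimulation site) white matter integrity alterations". The groups compared are responders and non-responders.

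The method is under Structural connectivity analysis. Each tract is resampled with an "elastic model with 30 points in space at analogous anatomical locations in each individual". Mean FA is computed at every point "to check for local differences at specific points of the tract". The section then closes with the model: "A linear mixed-effects model will be applied serially for each tract and permutation methods will be performed to adjust the". What is adjusted there is the set of p values, with type 1 error control as the aim.

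The article lists no fixed effects for that model. It states no test on the tract average, no group-by-position test, and no rule for labelling a result global or focal.

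**The concern.** Focal is a comparative claim: the group difference is larger in one part of the tract than in another. A set of point tests does not examine that comparison. If some points cross the threshold and others do not, reading the pattern as focal takes non-significance at the remaining points as evidence of no difference there. With about 35 patients split roughly 14 to 21, that step is weak. Adjusting p values over the points controls false positives at individual points but does nothing for the comparison between points. By raising the threshold it makes incomplete patterns more likely.

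At stake is how the primary result is interpreted. A patchy profile could be presented as an abnormality at the stimulated site when the data are equally compatible with the same difference along the whole tract.

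**Working it through.** **Inputs from the Protocol article.** 30 points per tract; alpha 0.05 and power 0.80; 32 active-arm patients, raised to 35 for 10% drop-out; a 40/60 split giving 14 responders and 21 non-responders. Applied to 32 patients, the split is 0.40 × 32 = 12.8, so about 13 v 19. The sample-size text reads "assuming an α risk of 0.05 and a 1-β power of 0.80, we estimated the need to include 32 patients for the active rTMS group", but gives no FA difference or SD, so the 32 cannot be reproduced forward.

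**Effect implied by the 32 patients.** Two-sided testing is assumed. With the normal approximation, d = (1.960 + 0.842) × √(1/n₁ + 1/n₂).
- 16 v 16: 2.80 × √0.125 = 0.99 (1.02 with the t distribution).
- 13 v 19: 2.80 × √0.1296 = 1.01 (1.04 with t).
- In reverse, d = 1 gives 2 × 2.80² / 1² = 15.7, so 16 per group and 32 in total.

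Drop-out: 32 / 0.90 = 35.6, or 32 × 1.1 = 35.2, against the stated 35. This is close enough to pass over.

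**Why a uniform difference looks patchy.** At d = 1.01 and 13 v 19, one unadjusted point has 80% power by construction. As a conservative bound on adjustment, Bonferroni over 30 points has critical value 3.14, and power per point is Φ(2.80 − 3.14) = about 0.37. A max-t permutation adjustment is less strict when points are correlated, but power per point still falls below 80%. Which points cross the threshold is then largely chance.

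**Simulation.** The same true difference was set at all 30 points. Each point had a two-sample t test, with max-|t| permutation adjustment over the points (499 permutations), adjusted p ≤ 0.05, and 500-1000 trials per setting. The article gives no correlation between points, so AR(1), exchangeable and mixed structures were tried. Percentages are of trials with at least one significant point.

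Only part of the tract significant (1-29 points), d = 1.01, 13 v 19:

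| Correlation between points | Share |
|---|---|
| AR(1) 0.8-0.9 | 99-100% |
| AR(1) 0.95 | 91% |
| AR(1) 0.98 | 71% |
| Exchangeable 0.5 / 0.8 / 0.95 | 99% / 83% / 46% |
| Two mixed structures | 94% / 68% |

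- With 14 v 21 the share was 77-99% over the structures run. A separate run with AR(1) 0.8-0.95 gave 85-100%.
- At d = 0.8 the share was 85-100%; at d = 1.5 it was 32-69%.
- Significant at no more than half the points: 22-80% at d = 1.01.
- All significant points in the half nearest the temporo-parietal junction (TPJ): 5-13% at d = 1.01 and 9-24% at d = 0.8. In the nearest third: 3-7% and 5-14%.
- The opposite end was about as likely. For AR(1) 0.9 at d = 1.01, 25.8% were confined to one half or the other and 12.6% to the TPJ half, leaving 25.8 − 12.6 = 13.2% for the far half.

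**The alternative, on the same uniform difference** (13 v 19, d = 1.01). A t test on tract-mean FA detected it in 79% to more than 99% of trials, depending on correlation. A permutation test on profiles centred within patient, standing in for the group-by-position test, wrongly signalled variation along the tract in 4-6% of trials (3-7% over all settings run).

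**The case against.** The strongest reply is that the article does not say 30 point tests are the whole analysis. The mixed model is fitted per tract, and with 30 positions per patient it is the natural place for a group effect and a group-by-position term. Fixed effects and contrasts are details that a condensed article may leave to the full protocol or analysis plan, and the along-tract method is also referred to a cited source. This stands in part: the unlisted fixed effects alone would be no finding. What remains is that the article promises a specific distinction, and the one step it connects with location cannot deliver it.

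A reader might go further and infer that a uniform difference will usually be reported as focal at the stimulation site. The documents do not support that. No written rule equates fewer than 30 significant points with focal. The article's own meaning of focal is proximity to the site, and significance confined to the TPJ half is a minority outcome. Nor is there a pull towards that end, since the far end comes up about as often.

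It is also fair that the study calls itself exploratory, and that permutation adjustment, properly applied, protects the claim that FA differs somewhere on a tract. The weakness affects where the difference is said to lie, not whether one exists.

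**Conclusion.** The point holds in a limited form. As described, the point-by-point check does not support the global-versus-focal conclusion that the article draws from it. At the effect implied by its own sample size, most positive results from a uniform difference would be patchy over much of the plausible correlation range. This stops being true when points are almost perfectly correlated (46% at exchangeable 0.95) and can stop when the effect is much larger (32-69% at d = 1.5). Patterns that would falsely point to the stimulated end are less common but are not negligible for a conclusion the article names in advance.

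The figures rest on an assumed effect size, assumed correlation structures, and max-t point tests standing in for the unspecified permutation procedure. The logical point does not depend on them.

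**What to change.** State the per-tract mixed model with group, position and group-by-position as fixed effects and patient as a random effect, and set the reading rule in advance:

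1. **Global:** test the group effect on tract-mean FA.
2. **Focal:** require a significant group-by-position interaction, or one pre-specified contrast of the TPJ-end segment against the rest, with the points in that segment fixed beforehand. The interaction shows only that the difference varies; a claim about the stimulated site also needs the contrast to point that way. Tracts without a TPJ end, such as the parietal-prefrontal ones, can use the interaction only.
3. **Otherwise:** report the tract-mean difference with its confidence interval, say that variation along the tract was not shown (which is not proof of uniformity), and present the 30-point profile as description.

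This needs no new data and no new model, only wording. The cost is fewer focal claims, because power for the interaction is limited at this sample size, so a truly focal difference may go unlabelled.
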